### Baseline characteristics

Baseline characteristics of all patients will be outlined per treatment allocation in a baseline table describing the following variables: age, sex, medical history (atrial fibrillation/flutter, stroke, hypercholesterolemia, hypertension, myocardial infarction, cardiac valve insufficiency/stenosis/replacement, peripheral vascular disease, obstructive pulmonary disease, and immunocompromised), current smoking, specific medication (anticoagulants, antiplatelet, statin, ACE inhibitor, ß-blocker, and proton pump inhibitor) prior to stroke, disability prior to stroke on mRS, stroke severity on NIHSS, performance of a screening test for swallowing function, dysphagia, acute treatment (IV thrombolysis and anticoagulant antagonist therapy) and diagnosis at discharge (infarct, haemorrhage, TIA, or other). Outline of the table is displayed in the ‘Outline of figures and tables’ section (Table 
3). All variables will be presented categorized by treatment arm. Dichotomous variables will be displayed in percentage with the number of patients divided by the total number of evaluated patients. Continuous variables will be reported as means with standard deviations when normally distributed and in medians with interquartile ranges when they do not meet the criterion of being normally distributed, as assessed by the Kolmogorov-Smirnov test. For continuous variables, the number of patients evaluated will be presented in a footnote of Table 
3.

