### Summary study protocol

PASS is a multicenter prospective, randomized, phase III, open-label, blinded end-point superiority trial (PROBE) of standard care with preventive ceftriaxone treatment compared to standard care without preventive ceftriaxone. Adult patients with stroke (both ischemic and hemorrhagic), a score ≥1 on the National Institutes of Health Stroke Scale (NIHSS) and stroke onset within 24 hours were included
[8]. Patients were excluded in case of infection at admission, use of antibiotics within 24 hours before admission, previous hypersensitivity or anaphylaxis to cephalosporins or penicillin, subarachnoid hemorrhage, pregnancy or when death seemed imminent. Patients were randomly assigned to either ceftriaxone at a dose of 2 g, given every 24 h intravenously for 4 days, in addition to stroke-unit care, or standard stroke-unit care without preventive antibiotic therapy. Randomization was performed through ALEA (online software for randomized trials;
https://nl.tenalea.net/amc/ALEA/Login.aspx) and is based on a uniform distribution; weight of the arms is equal (1:1). Randomization is stratified according to study center (academic hospital, large non-academic hospital, or small non-academic hospital) and stroke severity (score on NIHSS 1 to 9 or >9) and performed by using random blocks with a maximum block size of 6; blocks of 2, 4 and 6 are made per stratum combination

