[9]. The study has a PROBE design, which implies that blinding is lost, but only as to treatment. Patient and physician were aware of treatment allocation; however, the assessors of outcome were not. Data were collected on admission, during hospital stay, and at 3 months by standardized case record forms. The primary outcome is functional outcome at 3 months follow-up, as assessed on the mRS during a structured telephone interview by a trained assessor blinded for treatment allocation. Secondary outcomes are death rate at discharge and at 3 months, infection rate during hospital admission, length of hospital admission, volume of post-stroke care, use of antibiotics during hospital stay, quality adjusted life years (QALYs) and costs. Safety outcomes are complications of treatment, Serious adverse events (SAEs) and suspected unexpected serious adverse reactions (SUSARs). In the initial trial protocol, we presented a binary logistic regression analysis on the dichotomized mRS (0 to 2 versus 3 to 6) as primary outcome, requiring a sample size of 3,200 patients, and a proportional odds model in a secondary analysis of the primary end point
[9]. Blinded for any of the outcomes, we have changed the primary analysis in PASS from a binary logistic to an ordinal logistic regression on the original mRS, enhancing statistical power. The adapted power analysis showed that with identical assumptions on the clinical effect, using a 0.05 two-sided significance level and 80% study power, 2,550 patients were needed
[9]. The analysis of dichotomized mRS data will now be the secondary analysis of the primary end point.

On 23 March 2014, all patients were included and the last follow-up is expected in June 2014. For the complete study protocol and update, we refer to previous publications
[6, 7].

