**Table 3 Tab3:** **Baseline characteristics**

Baseline characteristics	Ceftriaxone + standard care	Standard care
Age - years		
Male sex - % n/N		
Medical history - % n/N		
- Atrial fibrillation/flutter		
- Stroke		
- Hypercholesterolemia		
- Hypertension		
- Myocardial infarction		
- Cardiac valve insufficiency/stenosis/replacement		
- Peripheral vascular disease		
- Obstructive pulmonary disease		
- Immunocompromised		
Current smoker - % n/N		
Medication prior to stroke - % n/N		
- Anticoagulants		
- Antiplatelet		
- Statin		
- ACE inhibitor		
- Bèta-blocker		
- Proton pump inhibitor		
Disability prior to stroke - mRS *		
Stroke severity - NIHSS **		
Swallowing screening performed - % n/N		
Dysphagic patients - % n/N		
Acute treatment - % n/N		
- IV thrombolysis		
- Coagulant therapy		
Diagnosis at discharge - % n/N		
- Infarction		
- Hemorrhage		
- Transient ischemic attack (TIA)		
- Other		

*mRS, denotes modified Rankin Scale.

**NIHSS denotes National Institutes of Health Stroke Scale.

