### Assessment of primary outcome

A structured telephone interview with each patient was held at 3 months by one of three trained research nurses, blinded for treatment allocation, to assess the primary outcome on the mRS. This structured telephone interview was validated in an earlier study
[11].

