### Analysis of primary outcome

An ordinal regression model on the total range of the mRS will be performed as the first analysis of primary outcome, under the assumption of proportional odds
[7]. The distribution of primary outcome (for example, functional outcome on the mRS) in both treatment groups will be expressed in a histogram (Figure 
4). Both adjusted and unadjusted analyses will be performed and reported. In clinical trials, adjusting for prognostic covariates improves statistical power, can correct for imbalances in baseline prognostic variables and can reduce variability in data
[17, 18]. The choice of prognostic covariates is mostly based on imbalances across treatment groups, prognostic factors that are related to the primary outcome, or a combination of both
[17]. As the investigators are blinded for all outcome data until the statistical analysis plan is accepted for publication, we chose to use the most important prognostic factors for outcome after stroke: age, stroke severity on the NIHSS, history of stroke, history of diabetes, prior disability as defined on mRS, and stroke type
[19]. Stratification of randomization was performed according to both study center and stroke severity, so we will also include study center as a covariate. The second analysis of the primary endpoint, that is, the dichotomized score on the mRS (for example, favorable versus unfavorable, mRS 0 to 2 versus mRS 3 to 6), will be expressed as OR with 95% confidence intervals (CI; Table 
4). Results of the dichotomized approach will be compared to the results of the primary analysis of primary outcome.

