### Subgroup analysis of primary and secondary outcomes

We will perform the following sub-group analyses for the primary outcome: stroke type (infarction or hemorrhage), stroke severity (NIHSS 1 to 9 or NIHSS 10 to 30), time between stroke symptoms and start of the antibiotic treatment (0 to 12 h versus 12 to 24 h) and age. For the subgroup analysis of primary analysis of primary outcome, the single OR from the proportional odds model will be calculated for each subgroup separately. For the subgroup analysis of secondary analysis of primary outcome, we will tabulate the results and analyze them using the chi-squared test and presented as OR and 95% CI ((Table 
7: subgroup analysis of primary outcome). In addition to these predefined subgroup analyses, we will perform a larger set of exploratory additional analyses. For secondary outcomes, we will perform all the previous mentioned subgroup analyses (stroke type, severity, time to treatment, and age). In addition we will perform analysis on presence of a swallowing disorder, respiratory tract infections, and a urinary catheter.

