**Table 7 Tab7:** **Subgroup analysis of primary outcome**

	Ceftriaxone + standard care (n = …)	Standard care (n = …)	***P***	OR 95% CI
Favorable outcome (mRS* 0 to 2) - % n/N				
- Ischemic stroke				
- Hemorrhagic stroke				
- Transient ischemic attack (TIA)				
- Other				
Favorable outcome (mRS 0 to 2) - % n/N				
- NIHSS** 1 to 9				
- NIHSS 10 to 30				
Favorable outcome (mRS 0 to 2) - % n/N				
- time to treatment 0 to 6 h				
- time to treatment 6 to 12 h				
- time to treatment 12 to 24 h				

*mRS, denotes modified Rankin Scale.

**NIHSS denotes National Institutes of Health Stroke Scale.

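### Diagnosis at discharge is shown as a baseline characteristic and supplies the stroke-type rows of Table 7, which contradict the two-level subgroup in the text and can depend on early recovery.

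*SAP article*

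**What the plan says.** All references are to the SAP article.

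- **Baseline characteristics and Table 3.** The baseline list ends with "diagnosis at discharge (infarct, haemorrhage, TIA, or other", and Table 3 carries it as "Diagnosis at discharge - % n/N". No other stroke-type variable appears in either place.
- **Subgroup analysis of primary and secondary outcomes.** The text defines the subgroup as "stroke type (infarction or hemorrhage", which is two levels.
- **Table 7.** The table prints four rows for the same factor: ischaemic stroke, haemorrhagic stroke, "Transient ischemic attack (TIA") and other.
- **Analysis of primary outcome.** The covariates of the adjusted model end with "prior disability as defined on mRS, and stroke type". The source, timing and number of levels of stroke type are not given. Adjusted and unadjusted results are both to be reported, and neither is named as the primary one.
- **Summary study protocol.** Entry was for "Adult patients with stroke (both ischemic and hemorrhagic"), with NIHSS of at least 1 and onset within 24 hours. The section also says: "Patient and physician were aware of treatment allocation". The three-month mRS, by contrast, is scored by research nurses "blinded for treatment allocation, to assess the primary outcome on the mRS".

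**The concern.** A baseline variable should be fixed before randomisation, or at least be beyond the reach of treatment and of knowledge of the allocation. A diagnosis recorded at discharge is fixed afterwards. For haemorrhage versus no haemorrhage this matters little, because that distinction is normally settled at presentation. For TIA versus infarction it matters more. Taking TIA in its ordinary sense (the article does not define it), a patient who entered with a measurable deficit and leaves labelled TIA is one whose deficit went away. The label is then an early relative of the mRS. Other is likewise a later judgement that the event was something else.

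Splitting patients on such a label removes good-outcome patients from the ischaemic row. If the two arms lose different proportions, the row compares groups that randomisation did not create. The TIA row itself will hold mostly favourable outcomes and say little. The same reasoning would apply to a regression that adjusts for the label.

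Apart from any bias, the text and Table 7 define different subgroups, so the planned analysis is not fixed.

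**Working it through.** **Step 1: where the four categories come from.** The rows of Table 7 match the discharge diagnosis category for category. The entry criteria admit ischaemic and haemorrhagic stroke, so TIA and Other are not entry categories. Rows with those names must therefore rest on a diagnosis settled after entry. For Table 7 the link to the discharge diagnosis is strong. For the covariate in the adjusted model it is an inference only.

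**Step 2: size in a Table 7 row.** The plan gives no TIA share and no mRS distribution, so there is no figure of its own to reproduce. Every input here is an assumption.

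- mRS 0 to 6 distributed 12/22/18/14/12/6/16% in both arms, so the true odds ratio is 1.00.
- 1,275 patients per arm (2,550 / 2).
- Only patients with mRS 0 or 1 (12 + 22 = 34%) can be labelled TIA. A fraction q of them is, so the TIA share is t = 0.34q.
- All non-TIA patients are treated as one row, standing in for the ischaemic row.

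Favourable outcome (mRS 0 to 2) is 12 + 22 + 18 = 52%. After the TIA patients are removed, the odds of a favourable outcome in an arm are (0.52 − t) / 0.48. The odds ratio in the row is therefore

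OR = (0.52 − t_ceftriaxone) / (0.52 − t_control).

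With t_control = 0.34 × 0.10 = 0.034:

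| t ceftriaxone | Dichotomised OR, non-TIA row | Proportional-odds OR, non-TIA row | Proportional-odds OR adjusted for TIA |
|---|---|---|---|
| 0.034 | 0.486/0.486 = 1.00 | 1.00 | 1.00 |
| 0.34 × 0.13 = 0.044 | 0.476/0.486 = 0.98 | 0.98 | 0.98 |
| 0.34 × 0.15 = 0.051 | 0.469/0.486 = 0.965 | 0.96 | 0.96 |
| 0.34 × 0.20 = 0.068 | 0.452/0.486 = 0.93 | 0.93 | 0.93 |

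The last two columns come from maximum-likelihood proportional-odds fits to the expected cell counts. The unadjusted odds ratio over all patients is 1.00 in every scenario. If ceftriaxone patients were labelled TIA less often than controls, the distortion would run the other way.

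**Step 3: a second set of assumptions.** Take 60% favourable in both arms overall, 95% favourable among TIA, and TIA shares of 5% versus 8%. The favourable proportion in the non-TIA row is f = (0.60 − 0.95t) / (1 − t).

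- Control: 0.5525/0.95 = 0.582, odds 0.5525/0.3975 = 1.390.
- Ceftriaxone: 0.524/0.92 = 0.570, odds 0.524/0.396 = 1.323.
- OR = 1.323/1.390 = 0.95, inside the range found in Step 2.

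**Step 4: after pooling.** If infarction, TIA and other form one level, moving a patient among them does not change the level. In the Step 2 setting both arms keep 52% favourable and the odds ratio is 1.00.

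**The case against.** The strongest reply is that much of the harm rests on inference.

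- **Covariate.** A reader might infer that the adjusted primary model conditions on early recovery. The article does not say so: it names stroke type without a source. The baseline list is also not a full inventory of covariates, because history of diabetes is adjusted for and is missing from that list too. An admission classification may exist in material not shown. This stands, and the covariate part can be put only conditionally.
- **Assessor.** A reader might infer that an unblinded treating physician makes the discharge diagnosis. The article says that physicians knew the allocation, but not who assigns this label. This stands.
- **Mechanism.** The trial expects benefit through fewer infections, which gives no evident reason to turn an infarct into a TIA. The Discussion mentions neuroprotection, but as a finding at least in animal studies. With entry allowed up to 24 hours after onset, there may be little time for treatment to change the label. This limits the likely size. It does not make a discharge label a baseline variable.
- **Subgroup text.** The two levels in the text are little affected, and the four rows occur only in the table. That is correct, but the two places then contradict each other, and Table 7 is what would be filled in.
- **Remedy.** Pooling TIA and Other with infarction is not exactly the dichotomy named in the text. This is correct and is a cost of the fix.

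**Conclusion.** The point holds in a limited form. The article presents a post-randomisation diagnosis as a baseline characteristic. Table 7 splits patients on the same categories, contrary to the subgroup text. If TIA or Other labelling differs by arm, the ischaemic row of Table 7 is not a randomised comparison. The adjusted model shares the problem only if its stroke-type covariate is the discharge diagnosis.

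The size is probably small: an odds ratio of about 0.93 to 0.98 where the truth is 1.00, and no bias if labelling is equal. These figures rest wholly on assumed TIA shares (3.4% in controls against 4.4% to 6.8% on ceftriaxone) and an assumed mRS distribution.

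The documents do not support a claim that the trial's main result is biased. The unadjusted intention-to-treat odds ratio is untouched, neither analysis is designated as primary, and nothing shows that labelling will in fact differ between arms. The change is worth making because it is cheap and can be made before the code is broken.

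**What to change.** 1. State the source, timing and levels of stroke type for both the covariate and the subgroup.
2. In Table 7 and in the adjusted model, use two levels: haemorrhage versus no haemorrhage. Take them from the admission diagnosis or imaging where recorded. Otherwise form them by pooling infarction, TIA and other.
3. Delete the TIA and Other rows from Table 7, and align the subgroup text and the table on the same two levels.
4. Report diagnosis at discharge descriptively by arm, apart from the baseline variables. This also shows whether TIA or Other labelling differed.

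The cost is SAP and table wording, with no new data. The factor is slightly coarser, and the non-haemorrhage group will include TIAs and non-strokes. Where only the discharge diagnosis exists, the pooled factor is still recorded late, but the recovery-dependent split is gone.

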**Table 3 Tab3:** **Baseline characteristics**

Baseline characteristics	Ceftriaxone + standard care	Standard care
Age - years		
Male sex - % n/N		
Medical history - % n/N		
- Atrial fibrillation/flutter		
- Stroke		
- Hypercholesterolemia		
- Hypertension		
- Myocardial infarction		
- Cardiac valve insufficiency/stenosis/replacement		
- Peripheral vascular disease		
- Obstructive pulmonary disease		
- Immunocompromised		
Current smoker - % n/N		
Medication prior to stroke - % n/N		
- Anticoagulants		
- Antiplatelet		
- Statin		
- ACE inhibitor		
- Bèta-blocker		
- Proton pump inhibitor		
Disability prior to stroke - mRS *		
Stroke severity - NIHSS **		
Swallowing screening performed - % n/N		
Dysphagic patients - % n/N		
Acute treatment - % n/N		
- IV thrombolysis		
- Coagulant therapy		
Diagnosis at discharge - % n/N		
- Infarction		
- Hemorrhage		
- Transient ischemic attack (TIA)		
- Other		

*mRS, denotes modified Rankin Scale.

**NIHSS denotes National Institutes of Health Stroke Scale.

### Assessment of primary outcome

A structured telephone interview with each patient was held at 3 months by one of three trained research nurses, blinded for treatment allocation, to assess the primary outcome on the mRS. This structured telephone interview was validated in an earlier study
[11].

### Assessment of secondary outcomes

The assessment of secondary outcomes will be performed as described below, for each outcome separately:

#### Infection rate during hospital admission

The total number of patients diagnosed with one or more infection(s) during hospital admission will be reported, as well as the total number of infections. Infections will be reported according to subtypes pneumonia, urinary tract infection and other infection. Infection will be assessed in two ways. First, the infection will be diagnosed in the clinical setting by the treating physician and registered as pneumonia, urinary tract infection or other infection. The clinical diagnosis of infection will be used for the primary analysis. Suspected infections without diagnostics being performed are also recorded and reported as such (for example, in a patient with a palliative care policy). Second, infection will be categorized by two infectious disease specialists who are blinded for treatment allocation, using the modified criteria of the Centers for Disease Control and Prevention (CDC criteria)
[12]. For this second categorization, patients with fever, new onset delirium or clinical diagnosis of infection during hospital admission will be reviewed. For this purpose, data on the diagnostic procedures during admission as recorded in the Case Record Form (CRF) will be used. For the diagnosis of pneumonia and urinary tract infection prespecified algorithms will be used based on the CDC-criteria (Figures 
2 and
3). Patients with a positive blood culture or a positive culture from the presumed site of infection, other than the lungs or urine, with a clinically relevant pathogen will be diagnosed as ‘other infection.’ Patients will be categorized as having confirmed pneumonia, urinary tract infection, or other infection. Only bacterial infections will be assessed since preventive antibiotic therapy aims to reduce these infections. Infection with *Clostridium difficile* is reported as a treatment complication. Case definition of this infection is diarrhea plus a positive *C. difficile* toxin test. Clostridium infection was diagnosed by the treating physician and was reviewed by the expert panel.

**Figure 2 Fig2:**
[figure not shown]
**Diagnosis of pneumonia.**

**Figure 3 Fig3:**
[figure not shown]
**Diagnosis of urinary tract infection.**

#### Death rate at discharge and at 3 months

Death during hospital admission was recorded in the CRF by the treating physician and notified as an SAE to the trial office. Death was also registered at the 3 months follow-up. If needed, survival status at 3 months was evaluated through contact with general practitioners and the municipality register.

#### Length of hospital stay

The day of admission and discharge was recorded in the CRF by the treating physician. Length of hospital admission is measured in days.

#### Total use of antibiotics during hospital stay

The use of antibiotics other than preventive antibiotic therapy will be recorded in the case record form. Total antibiotic use will be recorded in units of the ‘defined daily dose’ (DDD) and the number of days of use. For definitions of the DDD, classification according to the World Health Organization (WHO) will be used for each antibiotic
[13].

#### Volume of post-stroke care, cost-effectiveness analysis

The cost-effectiveness will be measured by an economic analysis conducted alongside the study. This analysis is not included in the publication to which this analysis plan applies.

### Assessment of safety outcomes

Safety outcomes are complications of treatment, SAEs and SUSARs. All SAEs and SUSARs during the hospital stay are recorded in case record forms by the treating physician and reported to the trial office. SAEs and SUSARs occurring after discharge are recorded during the follow-up interview at 3 months. The physician records treatment complications in the CRF (diarrhea caused by *C. difficile*, allergic reaction that caused cessation of ceftriaxone, infection with ceftriaxone resistant microorganism, phlebitis at place of IV-catheter, elevation of liver enzymes, oliguria or elevation of serum creatinine).

Cause of death will be reviewed by two independent observers. They will use information from the hospital discharge letter or the medical correspondence received by the general practitioner in case the patient died after discharge. Discrepancies will be reviewed in a consensus meeting in the presence of a third investigator. Outcome parameters were derived from three recent cardiovascular trials and were modified for expected outcomes in our study
[14–16]. A distinction will be made among a cardiovascular cause (brain infarction, brain hemorrhage, myocardial- or pulmonary embolism. or another cardiovascular cause), an infection (pneumonia, sepsis or another infection), death by any type of malignancy, death by any other cause (for example, traffic accident), withdrawal of treatment due to a poor prognosis or unknown cause of death.

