### Analysis of secondary outcomes

The number of patients with one or more in-hospital post-stroke infection(s) will be presented as numbers with event of numbers evaluated and analyzed using the chi-square test, and OR estimates with 95% CI. Infection rates will be reported as ‘judged by treating physicians’ and ‘infectious diseases panel.’ Death rate at discharge and at 3 months will also be analyzed using the chi-squared test and presented as OR estimates and 95% CI. Use of antibiotics in defined daily doses and length of hospital admission will be analyzed using the two group t-test or Mann- Whitney test where appropriate (Table 
4). The analysis of volume of post-stroke care, use of antibiotics during 3 months follow-up and the cost-effectiveness analysis will be analyzed using a separate analysis protocol and presented in a subsequent paper and is, therefore, not discussed here.

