**Table 5 Tab5:** **Number and type of serious adverse events**

Type of SAE* -% n/N	Ceftriaxone + standard care (n = …)	Standard care (n = …)	***P***
- Death			
- Life-threatening event			
- New hospitalization			
- Prolongation of existing hospitalization			
- Persistence of significant disability or incapacity			
Total number of SAE’s			

*SAE, serious adverse event.

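### No stated route brings C. difficile or resistant infections arising after discharge into the matching rows of Table 6; serious ones are still counted in Table 5, but not by diagnosis

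*SAP article*

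**What the plan says.** Assessment of safety outcomes names three safety outcomes: complications of treatment, SAEs and SUSARs. Two of them have a capture route for each phase. In hospital: "All SAEs and SUSARs during the hospital stay are recorded in case record forms by the treating physician and reported to the trial office". Afterwards: "SAEs and SUSARs occurring after discharge are recorded during the follow-up interview at 3 months". For complications the text says only "The physician records treatment complications in the CRF", followed by the list that becomes the rows of Table 6. It gives no observation period and does not mention the interview.

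The section on infection rate during hospital admission states that C. difficile infection "is reported as a treatment complication". It then adds: "Clostridium infection was diagnosed by the treating physician and was reviewed by the expert panel".

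The Safety outcomes section tabulates complications, SAEs and SUSARs by arm with a chi-squared test. Neither that section nor Table 6 gives a period. Table 5 has rows for degrees of seriousness, such as "Prolongation of existing hospitalization", death and new hospitalization. It has no row for a diagnosis.

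**The concern.** C. difficile diarrhoea and infection with a resistant organism can appear after an antibiotic course has ended, so part of the time at risk may fall after discharge. The section on protocol deviations accepts discharge as a reason for ending the course within 4 days, so some patients leave hospital observation very early.

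If Table 6 is in effect an in-hospital table, three things follow.

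- Function and death are followed to 3 months, while the drug-specific harms are followed for a shorter and variable time.
- The count depends on length of stay. The Discussion suggests that ceftriaxone might shorten the stay. If it did, the ceftriaxone arm would be observed for less time, which would lower its count.
- A late readmission for C. difficile would be counted in Table 5 as a new hospitalization, where a reader could not recognize it as a harm of the antibiotic.

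The table carries P values. A counting rule left open could be settled after the code is broken.

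**Working it through.** **Step 1. Capture routes, set side by side** (Assessment of safety outcomes; Infection rate during hospital admission; Tables 5 and 6)

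| Event | In hospital | After discharge | Where it is shown |
|---|---|---|---|
| SAE, SUSAR | Treating physician, CRF, trial office | 3-month interview | SAEs in Table 5, by seriousness |
| Complication that is not an SAE | Physician, CRF | None stated | Table 6 |
| Complication that is an SAE | Both routes | 3-month interview, as an SAE | Table 5; no stated rule carries it into Table 6 |

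The person doing the recording also differs. Complications are recorded by the physician. Assessment of primary outcome describes the 3-month telephone interview as held by research nurses. C. difficile is described as diagnosed by the treating physician, under a heading limited to the admission. These points together make in-hospital capture the natural reading. None of them states it.

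**Step 2. Illustration of size**

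The plan gives no complication rates, so it has no figure to reproduce.

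- From the plan: 2,550 patients randomized 1:1, so 2,550 / 2 = 1,275 per arm; chi-squared test; two-sided 0.05 (the level given for the primary analysis).
- Assumed: C. difficile by 3 months in 1.0% versus 0.2%; the same late share L in both arms; every late event missing from Table 6.

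Expected count in Table 6 = 1,275 × rate × (1 − L).

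- L = 0: 1,275 × 0.010 = 12.75 and 1,275 × 0.002 = 2.55, an excess of 10.2 cases.
- L = 0.5: 6.4 and 1.3, an excess of 5.1 cases.

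The expected ratio stays at 5 to 1. The absolute excess and the power fall.

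Power by exact enumeration of the two binomial counts:

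| Late share L | Chi-squared, uncorrected (planned test) | Fisher exact |
|---|---|---|
| 0 | 78% | 70% |
| 0.3 | 60% | 49% |
| 0.5 | 46% | 31% |
| 0.7 | 28% | 10% |

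The chi-squared column is the relevant one, because the Safety outcomes section specifies that test. The Fisher column is shown because the counts are small.

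**Step 3. Check by normal approximation**

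Power = Φ[(p1 − p2 − 1.96 × SE0) / SE1], where SE0 uses the pooled rate and SE1 the separate rates.

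- L = 0: (0.008 − 1.96 × 0.003059) / 0.003055 = 0.656, power 74%.
- L = 0.5: (0.004 − 1.96 × 0.002166) / 0.002165 = −0.113, power 46% (0.455).

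**Step 4. Other assumed rates, same approximation, L = 0 to L = 0.5**

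- 1.0% versus 0.5%: 31% to 18%.
- 2.0% versus 0.5%: 93% to 67%.

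**The case against.** A reader might infer that late C. difficile and resistant infections never reach Table 6 and that ceftriaxone's delayed harms are undercounted as a matter of fact. The document does not say so. The sentence on complications sets no discharge limit. CRFs were not confined to the admission: "Data were collected on admission, during hospital stay, and at 3 months by standardized case record forms". Nor are SAEs and SUSARs the only data collected after discharge. Function and death are assessed at 3 months, and the plan refers to "use of antibiotics during 3 months follow-up", to be reported in a separate paper. The protocol and the CRF, not shown here, may define the window. All of this stands, and it limits the point to a natural reading.

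Serious late harms are also not lost. They are recorded at the interview, tabulated by arm and tested in Table 5, and the 3-month functional and mortality outcomes include their consequences. The infection benefit is itself counted only in hospital, so the contrast between long follow-up for benefit and short follow-up for harm is not complete. Most other rows of Table 6, such as phlebitis or an allergic reaction that stops treatment, mainly concern the treatment period. This stands too.

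The Discussion says only that benefit might come partly through a shorter stay; it does not predict one. The power figures rest on assumed rates, and the plan claims no power for any row of Table 6.

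The objection does not remove the gap between the two tables. The SAP sets out how each safety outcome is captured and how both tables are laid out. Nothing in it says that a post-discharge SAE with a matching diagnosis is counted in Table 6. That is an analysis rule, and it belongs in this document.

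**Conclusion.** The point holds in a limited form. The plan names a post-discharge route for SAEs and SUSARs but none for treatment complications, and Table 5 does not show diagnoses. On the most natural reading, C. difficile and resistant infections arising after discharge would be absent from their Table 6 rows, while serious ones would still be counted in Table 5. Non-serious late cases have no stated route at all.

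The size of any undercount cannot be derived from the document. The fall in power from about 78% to about 46% assumes rates of 1.0% versus 0.2%, half the events after discharge, an equal late share in both arms and no late event entered in Table 6. It shows what could be at stake and does not estimate what will happen.

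The change should be made because it is cheap, uses data already recorded, and makes the comparison of drug-specific harms more complete and less dependent on length of stay.

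**What to change.** - Code by diagnosis the post-discharge SAEs already recorded at the 3-month interview, blind to allocation. Count C. difficile and resistant infections among them in the matching rows of Table 6.
- Show in-hospital and post-discharge counts separately in Table 6, and state that a patient may appear in both Table 5 and Table 6.
- Add a breakdown by diagnosis to Table 5.
- Label Table 6 with its observation period. If the CRF already asks about complications at 3 months, say so.
- Footnote that non-serious post-discharge events, and events without laboratory confirmation, are incompletely captured. The case definition of C. difficile needs a positive toxin test, which an interview may not supply.

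The fix should not rely on general-practitioner letters for all patients, because the plan describes that correspondence only for patients who died after discharge.

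The cost is modest extra coding and a few more columns and rows. No new patient contact is needed. The remaining weakness is uneven completeness after discharge, which the separate counts and the footnote make visible.
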